# Research Plan and Methods

The proposed study will involve quantitative analysis of primary quantitative data from household interviews and health facility exit interviews.

## Primary Data Collection and Analysis

### Study Sites

Primary data collection will take place in the Kilombero district in the Morogoro region, and Same district in the Kilimanjaro region. Both regions are primarily rural with a town center at Ifakara and Same town, respectively. Kilombero District was chosen due to the long-standing research collaborations with IHI in Kilombero as Ifakara is the main field center. Same district was selected because of the similar health care infrastructure including number of hospitals, health facilities, and dispensaries, and similar rural/urban mix as Kilombero, but with differing health policies as it is located in a different region. The study will take place at both healthcare facilities and in private households throughout the two districts.

### Study Design

This study will use primary data that will be collected in two surveys: A general household survey including biometric testing for hypertension and diabetes, and an exit questionnaire administered to patients following their visit at a health facility.

### Sampling Strategy and Sample Size

#### *Household survey*

We will conduct a household survey to collect information on household demographic and economic characteristics, health insurance and social protection, chronic illness, healthcare access and utilisation, household health expenditure, out of pocket payments for health care, and coping strategies to deal with diseases. In order to answer the key research question, information will be collected regarding direct and indirect household out-of-pocket expenditure (OOPs) on healthcare, how the household pays for their OOPs or social health protection premiums, economic productivity loss due to illness, recent healthcare utilisation, and the role of one’s social network in coping with illness. For respondents that accept, we will also measure blood pressure and random blood sugar to quantify undiagnosed and untreated hypertension and possible diabetes in the population. We will counsel patients with results outside of the normal range of the importance of following up with a healthcare provider to formally diagnose and initiate treatment if needed.

Using a stratified sampling approach, a household survey will be delivered throughout Kilombero and Same districts. In order to detect associations with the primary outcome of household health expenditure (power of 0.80, significance level of 0.05), a minimum sample size of 202 households per district is required. To calculate the minimum sample size, a household health expenditure of 30,000 Tanzanian shillings was used as a benchmark; corresponding to the cost of enrolling a household in the iCHF. However, in order to also answer research questions associated with our secondary objectives, we will seek a total sample size of 390 households per district.

As such, in each of Kilombero and Same district, 15 households from each district’s only town (Ifakara and Same, respectively), and 15 households from a random selection of 25 other villages will be sampled (Table 1).

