It is expected that with 2 field workers per health facility, 36 patients can be interviewed per day at hospitals and health centres, while 1 one field worker is expected to be able to interview 12 patients per day at each sampled dispensary. If patient volume is too low to meet this daily requirement, field workers will return later to the same facility to ensure the sample size is reached. As such, across both districts, we are anticipating a total sample size of 1,632 for the exit survey (Table 1), generously exceeding the minimum sample size that was previously indicated. Participants will be recruited while waiting to enter the consultation room, and the research assistant will administer the questionnaire after the participants has seen the clinician so as to avoid disrupting the work flow at the clinic.

The questions asked in the exit survey will mostly be the same as those asked in the household survey, so that household survey respondents will serve as the general population with which people accessing NCD care can be compared. However, in the exit surveys, additional questionnaire items will be included relating to the specific services being utilised on the day of the health facility visit. The questionnaire will take on average 20 minutes to complete. If during the piloting phase the questionnaire takes too long to complete, we will reduce the number of questions asked from the accepted survey, prioritizing questions that best reflect the explicit research questions.

**Table 1: Sample size and sampling strata.** Sample size calculated based on a hypertension prevalence of 19.9% (95% CI: 17.1-22.9) for rural Tanzania [11], population estimates from the Tanzania 2012 census, and a benchmark mean annual household health expenditure of 30,000 Tanzanian shillings by using a modified Cochran sample size calculation.

| **Study Type** | **Sample Size** | **Strata** |
| --- | --- | --- |
| Exit Interviews |  | Kilombero District:   - 18 health facilities |
|  | 72 per hospital | - 2 hospitals |
|  | 72 per health centre | - 8 health centres |
|  | 12 per dispensary | - 8 dispensaries |
|  |  | Same District:   - 18 health facilities |
|  | 72 per hospital | - 2 hospitals |
|  | 72 per health centre | - 8 health centres |
|  | 12 per dispensary | - 8 dispensaries |
|  | **Total: 1,632** | **Total: 36 health facilities** |
| Household Survey |  | Kilombero District: |
|  | 15 households | Ifakara town |

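### The 80% power claimed for 202 households per district on household health expenditure cannot be derived from the calculation and inputs the protocol names

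*Protocol*

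**What the plan says.** The Household survey section (under Sampling Strategy and Sample Size) makes a power claim for the named primary outcome. It sets, for detecting "associations with the primary outcome of household health expenditure (power of 0.80, significance level of 0.05), a minimum sample size of 202 households" per district. On inputs, the same section says that "a household health expenditure of 30,000 Tanzanian shillings was used as a benchmark", and explains that level as "corresponding to the cost of enrolling a household in the iCHF". The target is then raised to 390 households per district so that secondary objectives can also be answered. These come from 15 households in one town and 15 in each of 25 villages.

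The method appears only in the Table 1 caption, under Exit survey. It begins "Sample size calculated based on a hypertension prevalence of 19.9"% (95% CI 17.1 to 22.9), adds 2012 census population estimates, and ends with "a benchmark mean annual household health expenditure of 30,000 Tanzanian shillings by using a modified Cochran sample size calculation".

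Neither place gives an SD of expenditure, a difference to detect, an exposure or comparison, a margin of error, a description of the modification, or a design effect.

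**The concern.** A power statement needs an outcome variance, an alternative and a comparison. The document gives a power figure for expenditure and attributes the sample size to a method that uses none of these. This is more than detail left to an analysis plan: the protocol states a specific design property, names how the size was obtained, and the two do not fit.

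It is the only power statement for the primary outcome. Analytical Methods plans models of expenditure on distance and on social health protection, and Research Question 1 compares costs between NHIF members, iCHF members and people in no scheme. Ethics bodies and later readers would take it that such associations are covered at 80% power. The protocol does not say for which association, or for what size of difference, that would be true.

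**Working it through.** **Inputs from the protocol.** Power 0.80; alpha 0.05 (taken as two-sided, since sidedness is not stated); minimum 202 and target 390 households per district; prevalence 19.9%; benchmark 30,000 shillings; 15 households per site. The census figure used is not given.

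**Step 1: can 202 be reproduced as a Cochran size?** For a proportion, n = z²p(1−p)/e².
- At e = 0.05: 1.96² × 0.199 × 0.801 / 0.05² = 244.9, so 245. Over the prevalence interval (17.1% to 22.9%) the result runs from 218 to 271.
- A finite-population correction brings 245 down to 202 only if N = (245 − 1)/(245/202 − 1), about 1,150 units. That looks too small for a district with a town and more than 25 villages, but this is a judgement because the census figure is not shown.
- At e = 0.055: 202.4. The protocol states no such margin; it is found only by solving backwards.

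For a mean, n = (z × SD/e)². This needs an SD and a margin, and neither is given. Neither form contains beta.

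**Step 2: can 202 be reproduced as a power calculation?** Write k = 1.960 + 0.842 = 2.802.
- One-sample mean: the standardised difference is k/√202 = 0.197. An assumed 0.2 gives n of about 197, close to 202. No such effect is stated, and a test of one mean against a benchmark is not a test of association.
- One-sample proportion at 19.9%: k² × 0.199 × 0.801 / e² gives 500 at 5 points and 195 at 8 points.

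The stated inputs do not determine 202 by either route.

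**Step 3: what the sample sizes would detect.** For two groups with fractions f and 1−f, the smallest difference detectable at 80% power is k/√(n f(1−f)) in SD units. The splits are assumptions. The 32% and 7% are the national coverage figures in Statement of Problem, and 19.9% is the cited rural prevalence. The protocol names none of them as the primary comparison.

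| Assumed split | n = 202 | n = 390 |
|---|---|---|
| 50/50 | 0.39 | 0.28 |
| 32/68 | 0.42 | 0.30 |
| 19.9/80.1 | 0.49 | 0.36 |
| 7/93 | 0.77 | 0.56 |

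Conversely, with 202 households, power at 0.2, 0.3 and 0.4 SD is 30%, 57% and 81% for equal groups, and 20%, 40% and 62% for the 19.9/80.1 split. In money, if the SD were 1, 2 or 3 times 30,000 shillings (assumed), 0.39 SD would be about 11,800, 23,700 or 35,500 shillings.

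**Step 4: clustering.** With 15 households per site, the design effect is 1 + 14 × ICC. The ICC is assumed:
- ICC 0.01: design effect 1.14; 390 acts like 342.
- ICC 0.05: design effect 1.70; 390 acts like 229.
- ICC 0.10: design effect 2.40; 390 acts like about 163.

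Multiplying the n = 390 column by √1.70 = 1.304 gives 0.28 × 1.304 = 0.37 SD for equal groups and 0.355 × 1.304 = 0.46 SD for the 19.9/80.1 split. Over ICC 0.01 to 0.10 the ranges are 0.30 to 0.44 and 0.38 to 0.55 SD. This applies the full design effect. An exposure that varies mainly within villages would be penalised less.

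For both districts pooled (52 × 15 = 780), the same formula gives 0.20 and 0.25 SD before clustering, and 0.26 and 0.33 SD at ICC 0.05.

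**The case against.** The best defence is that the calculation is called modified and the modification is not described. An undisclosed power step may lie behind it, and Step 2 shows that an assumed one-sample effect near 0.2 comes close to 202. That stands. A reader might infer that the 202 cannot possibly rest on a power calculation; the document does not support so much. It supports only that the claim does not follow from the method and inputs named.

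Three other stronger readings are tempting and should be resisted:
- **That 202 is really a prevalence size at ±5.5 points.** The Household survey section ties 202 only to the expenditure benchmark. The caption covers both surveys, does not say which input produced which number, and the table does not contain 202.
- **That the protocol contradicts itself on what 30,000 shillings is.** An expenditure benchmark set at the level of the iCHF enrolment cost is compatible with the caption's description. The caption only adds that it is a mean and annual.
- **That the survey is underpowered.** No primary comparison, SD or target difference is fixed, so no shortfall can be computed. The planned 390 also exceeds 202 by 93%.

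The defence may add that the study is cross-sectional, starts with descriptive statistics and treats its association hypotheses as exploratory. That lowers the consequences but does not make the stated power correct. Nor does the larger target supply a basis, because the protocol justifies 390 by secondary objectives.

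**Conclusion.** The point holds in this limited form: the power of 0.80 attached to 202 households per district is not a property that the documented calculation can supply. It is a wrongly stated design figure rather than a mere omission. Its size cannot be expressed as one corrected sample size, because the quantities needed are absent. What can be shown is how widely the meaning of 80% power varies: from 0.39 to 0.77 SD at 202 households and from 0.28 to 0.56 SD at 390, across the assumed splits and before clustering. These figures rest on a two-sided test, equal SDs and simple random sampling. The clustered figures rest in addition on an assumed ICC. They illustrate the gap and do not describe a planned test.

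**What to change.** 1. In the Household survey section, either remove the power figure from the 202, or substantiate it with the comparison, SD and difference actually used, and say what was modified in the Cochran calculation.
2. For the planned 390 per district and 780 in total, state the smallest expenditure difference detectable at 80% power for one named comparison. Give the SD or work in SD units, and state the ICC assumed for clusters of 15. The 0.37 and 0.46 SD figures show the form such a statement would take; the sponsor's own inputs should replace them.
3. In the Table 1 caption, say which input served which survey and which number. The table's household total should also be reconciled: it prints 790, while 52 × 15 = 780.
4. Do not restate 202 as ±5.5 points on prevalence. The protocol gives no such margin, and the figure would ignore the clustering.

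The cost is a few sentences and no extra households. The stated property becomes less favourable than a plain 80%.

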The second research question will aim to quantify the direct and indirect cost associated with accessing NCD care services, and describe strategies for coping with the cost burden. This includes determining which support systems people living with NCDs utilise, including their social networks, to cope with these costs. It will also seek to determine the cost of not having social health protection by comparing the total costs incurred between NHIF beneficiaries, iCHF beneficiaries, and those who are not part of a social health protection scheme. The role of patient social networks will be especially important to investigate, as it has been reported that people often attempt to capitalise on their social networks to avoid out-of-pocket expenditure (OOPs) by being added to another household’s iCHF membership, or by borrowing money from their social network [8]. Furthermore, this objective will take into account that although beneficiaries of social health protection may be less likely to experience financial hardship due to the direct cost of their illness, their illness may still impose a social and economic burden in the form of missed work days and lost income for either the individual living with the NCD, or their caregiver at times when one’s illness prevents them from working [9].

### Research Question 2

The third research question aims to understand the differences between people with NCDs who are engaged in care and those that are not. We aim to identify the proportion of the population that remains undiagnosed, and undertreated for hypertension and diabetes, and the barriers or perceived barriers to appropriately utilising NCD treatment compared with the patients who are accessing NCD care. In addition to socio-demographic and geographic mediators of care utilisation, we will quantify the willingness-to-pay for chronic disease care under different payment options, specifically out-of-pocket payments versus the payment of health insurance premiums, for both patients and individuals in the community.

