### Analytical Methods

By delivering a household survey to the general populations of Kilombero and Same, and an exit survey to people accessing NCD services, we will be able to comparatively analyse the specific challenges and coping mechanisms that people living with NCDs face in accessing services, in relation to the general population.

The data collected from the household survey and exit survey will first be analysed using descriptive statistics to investigate the burden of OOPs and economic losses associated with living with hypertension and/or diabetes, and to determine how much households spend upon the direct and indirect costs of accessing NCD care. General hypotheses related to the geographic and economic accessibility of health care, such as whether distance from a health facility is associated with direct and indirect healthcare costs, and whether distance from a health facility moderates the association between social health protection and household health expenditure, will be explored using linear mixed models and analyses of variance.

We will quantify the proportion of the household survey respondents who were hypertensive or diabetic, and not aware of their condition or not enrolled in care. We will then use univariate and multivariate logistic regression analyses to identify differences between the household respondents with an NCD who are not enrolled in care and NCD patients from the exit interviews who are enrolled in care. We will quantify systematic and individual characteristic predictors of willingness-to-pay for NCD care and social health protection schemes for people in care for non-NCD reasons, for NCD reasons, and household respondents.

A regression model will then be used to assess whether living with hypertension and/or diabetes is associated with financial hardship, and/or illness-related economic and productivity losses, using the indicators catastrophic health expenditure and impoverishment. An analysis of variance (ANOVA) of mean spending by revenue source will then be used to determine the relative importance of financial contributions from various household revenue streams to covering the costs of NCD care, such as:

- Earnings from work (informal or formal)

- Selling personal property (clothing, bicycle, furniture, etc.)

- Financial contributions from the social network (friends, family, neighbours, etc.)

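### Fixing the town at 15 of 390 households per district makes the respondent proportion a biased estimate of the district population proportion, unless the town holds about 4% of households or town and village outcomes agree

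*Protocol*

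**What the plan says.** The Protocol's Household survey section sets the design: "Using a stratified sampling approach, a household survey will be delivered throughout Kilombero and Same districts". Each district has one town, which contributes 15 households; in addition, "15 households from a random selection of 25 other villages will be sampled". The section states the resulting target: "we will seek a total sample size of 390 households per district". Table 1 repeats the equal take. Neither place links the allocation or the choice of villages to population size. Table 1 cites 2012 census population estimates, but only as an input to the sample size.

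The target is a population quantity. Under Research Question 2 the study aims to "identify the proportion of the population that remains undiagnosed, and undertreated for hypertension and diabetes". The Household survey section says that blood pressure and blood sugar are measured to quantify disease in the population, and the Exit survey section uses the household respondents to represent the general population.

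The estimator is worded differently. The Analytical Methods say: "We will quantify the proportion of the household survey respondents who were hypertensive or diabetic", continuing to those unaware of their condition or not in care. Weights and selection probabilities are not mentioned anywhere in the Protocol.

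**The concern.** A stratified sample estimates a population proportion only if each stratum enters in proportion to its size or is weighted back to it. Here the town's share of the sample follows from the choice of 15 households per site, not from the town's population. Taken as written, the proportion of respondents gives the town 3.85% of the influence even if it holds several times that share of households.

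The Protocol itself gives reason to expect different outcomes in town and village. Its Introduction reports poor availability of NCD diagnosis and care outside the larger towns, and its Statement of Problem says that quality care is often missing at facilities serving non-urban areas. Access of that kind bears directly on whether a person is undiagnosed or untreated. At stake are the population figures for undiagnosed and undertreated disease, and any other simple population mean or proportion from the household survey.

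**Working it through.** **Reproducing the plan's figure.** One town and 25 villages give 26 groups of 15 households: 15 + 25 × 15 = 390 per district, as stated. (Two districts give 780; Table 1 prints 790, a separate slip that does not affect this point.)

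**Inputs.** From the Household survey section: n = 390 and town sample share s = 15/390 = 0.0385. From Table 1: rural hypertension prevalence 19.9%, used for the villages. Assumed, because the documents give neither: the town's true share of district households, t = 10, 20 or 30%, and the town-village difference d.

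**Bias.** The respondent proportion minus the population proportion is (s − t) × (town proportion − village proportion), so its size is (t − s) × d. For d = 10 points:

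- t = 10%: (0.10 − 0.0385) × 10 = 0.6 points
- t = 20%: (0.20 − 0.0385) × 10 = 1.6 points
- t = 30%: (0.30 − 0.0385) × 10 = 2.6 points

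Example: with 19.9% in villages and an assumed 30% in town, the respondent proportion is 20.3% in all three cases, while the population values are 20.9%, 21.9% and 22.9%. The bias is zero if t = 3.85% or d = 0. Its sign depends on the direction of the difference, which need not be the same for prevalence and for the undiagnosed share.

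**Cost of weighting afterwards.** A town household needs weight t/s and a village household (1 − t)/(1 − s), relative to a mean of 1. The Kish variance factor is t²/s + (1 − t)²/(1 − s).

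| Assumed t | Town weight ÷ village weight | Kish factor | Effective n of 390 |
|---|---|---|---|
| 10% | 2.8 | 1.10 | 354 |
| 20% | 6.3 | 1.71 | 229 |
| 30% | 10.7 | 2.85 | 137 |

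These factors come before any clustering effect.

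**Does weighting alone pay?** The Kish factor equals 1 + (t − s)²/[s(1 − s)]. The squared bias (t − s)²d² therefore equals the added variance when d² = p(1 − p)/[n s(1 − s)]. With p = 0.199 this is 0.1594/(390 × 0.03698) = 0.0111, so d = 10.5 points. Below that difference, weighting one district's 390 households removes the bias but does not reduce total mean squared error; above it, it does. The binding limit is the 15 town households, not the absence of weights alone.

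**Villages.** The Protocol calls the selection random without giving probabilities. Drawn proportional to size, 15 per village is roughly self-weighting among villages. Drawn with equal probability, large villages are under-represented. In a simulation with village prevalence averaging 19.9%, an assumed between-village SD of 6 points and an assumed size-prevalence correlation of 0.5, the equal-probability estimate was low by about 1.4 points (size coefficient of variation 0.5) to 2.1 points (0.8). It was essentially unbiased with no correlation, or with selection proportional to size.

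**The case against.** The strongest objection is that the documents do not establish as much as they may seem to.

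- A reader might infer that the plan prescribes an unweighted analysis. It does not use that word. Weights could appear in an analysis plan that is not shown, and their absence from the Protocol would not by itself be a finding. This stands, but an analysis plan cannot add town households: the allocation is a stated Protocol choice.
- A reader might infer that villages are drawn with equal probability. The text does not say so, and a fixed take per village is also what size-proportional selection would use. This stands; the village imbalance is conditional.
- A reader might infer that the study's main result is biased in a known direction. The primary outcome is household health expenditure, and the power statement ("power of 0.80, significance level of 0.05") concerns associations with it. The undiagnosed proportion is one part of Research Question 2, and regression associations are less exposed. The direction and size of the bias rest on assumptions. The Study Sites section describes the areas as mainly rural, and even 2.6 points is below the simple-random-sample half-width of 1.96 × √(0.199 × 0.801/390) = 4.0 points. All of this stands, though the bias does not shrink as n grows and the interval does not account for it.
- A reader might also object that 15 households cannot support a separate town estimate. The Protocol promises none, so this is not a defect.
- Wide village coverage has its own value, because distance from a facility is analysed as a predictor and moderator. This is a fair argument against full reallocation, but not against weighting the population proportions.

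**Conclusion.** The point holds for the population proportions. Followed as written, the plan gives the town 3.85% of the weight in an estimate meant for the whole district. That is correct only if the town holds about 4% of households or if town and village outcomes do not differ, and the Protocol's own background argues against the second condition. The size is modest to moderate: 0.6/1.6/2.6 points per 10-point difference at assumed town shares of 10/20/30%. Neither the shares nor the difference can be taken from the documents, so no direction or actual size can be claimed. The further imbalance among villages arises only if their selection is not proportional to size. The documents do not support extending the criticism to the regression associations or to the primary expenditure analysis as powered. It should be corrected, but it does not threaten the study.

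**What to change.** 1. For the population proportions, report design-weighted estimates using census household counts for the town and villages of each district, with intervals that allow for clustering by village. The regression associations need not be weighted. Failing this, describe the figures as applying to respondents only.
2. State how villages are drawn: proportional to size, or by another random method with each village's selection probability recorded and used in the weights.
3. If sites are not yet drawn, move some of the 26 groups of 15 to the town, roughly in line with its census share, keeping 390 per district. At an assumed 20% share, 5 groups give 75/390 = 19.2%, and the Kish factor falls from 1.71 to about 1.00.

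**Cost.** Items 1 and 2 need census household counts from a source that the Protocol already cites for population, and some analysis time. With only 15 town households they also carry the variance inflation of 1.10/1.71/2.85 shown above, so item 3 is worth doing where it is still possible. Full proportional allocation costs villages: at 20%, 26 × 0.20 ≈ 5 town groups leave 21 villages (4 fewer); at 30%, 26 × 0.30 ≈ 8 leave 18 (7 fewer). A partial shift combined with weighting is a reasonable compromise if village spread matters for the distance analyses.
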